### Study groups.

GROUP 1: Screening by annual FIT for three consecutive years and colonoscopy if the FIT result is

≥10 µg of Hb/g of faeces.

GROUP 2: Screening by one-time colonoscopy. In cases where a full colonoscopy cannot be carried out, CT colonography, capsule colonoscopy or barium enema will be offered instead.

### Selection process and screening invitation.

It will be held on a scheduled basis from index cases diagnosed of CRC during the previous 24 months at the Endoscopy Units of participating centres. After at least 3 months from diagnosis and once radiotherapy or oncologic surgery have been performed, the index case will be contacted by phone to arrange an appointment at the High Risk CRC Clinic (HRCC). In this clinic the patient will be informed of the study objectives and informed consent and permission to contact their FDRs will be requested.

If the patient agrees to participate and meets the inclusion criteria, a family tree of the first generation (parents, children or siblings) will be generated to identify all eligible and living FDRs. At this point, an open-label randomization (1:1) for the subject and investigator, to FIT for three consecutive years and work-up colonoscopy if a positive test versus straightforward colonoscopy will be performed, using the randomization module in RedCap Electronnic Data Capture (REDcap). All individuals will receive a letter signed by the medical coordinator who saw the index case in each hospital. This letter will describe the importance of CRC as a health problem in the population at familial risk and will provide information of the next study in FDRs of patients with CRC (cover letter). Later, a second letter will be sent, also signed by the medical coordinator of the study, in which the individual will be invited to participate in the randomized control study (invitation letter). The study aim and the screening option to which the individual has been assigned will also be included in this second letter. Finally, a phone number or email will be provided to request a visit to the HRCC of the corresponding hospital. Individuals who do not respond to the invitation letter after 2 months will be sent a second invitation letter.

Eligible FDRs that attend the HRCC to participate in the study will receive detailed information on the advantages and disadvantages of both tests. Participants with a negative FIT result will be sent an invitation letter to repeat the test. Crossover between groups will not be allowed.

### Study variables and procedures.

***Colonoscopy***: colonoscopies will be performed by experienced endoscopists who have performed > 200 scans and > 50 polypectomies in the previous year. Sedation and colon cleansing will be performed as previously described (Parra et al. World J Gastroenterol 2006). The Boston classification will be used as a scale for bowel cleansing and it will be considered to be adequate when the score is ≥ 2 points in each segment (Lai EJ, et al Gastrointest Endosc 2009). Each colon segment consists of "ascending colon and cecum", "transverse colon" and "descending colon, sigmoid and rectum ', amounting to a minimum of 6 points in the Boston classification (Lai EJ, et al Gastrointest Endosc 2009). Colonoscopy will be considered complete when cleansing is adequate and the cecum is reached. Otherwise the colonoscopy will be considered incomplete and shall be repeated.

***Polyp features:*** Polyp location will be recorded by segmentation. Polyp size and morphology will be recorded using the Paris classification (Gastrointest Endosc 2003:58, Suppl S3-S43). Whether the polyp was removed whole or by fragments will also be recorded. Lesions will be classified as distal or proximal to the splenic flexure. Adenomas ≥ 10 mm in size, with tubulovillous architecture, with high- grade dysplasia or *in situ* adenocarcinoma -pTis- will be considered to be advanced adenomas. Invasive CRC occurs when neoplastic cells cross the *muscularis mucosae*. Advanced neoplasia is the name given to advanced adenomas or invasive CRC. Serrated polyps will be classified according to the World Health Organization (WHO) classification as hyperplastic polyps, sessile serrated adenomas with or without dysplasia and traditional serrated adenomas. In patients with advanced adenoma >20 mm or with advanced adenoma resected in multiple fragments, a surveillance colonoscopy will be performed at 6-12 months after the previous colonoscopy.

#### Immunochemical Fecal Occult Blood Test (FIT):

Participants assigned to the FIT group will receive an annual automated quantitative FIT kit for three consecutive years. The threshold of 10 μg Hb/g faeces (equivalent to 50 ng Hb/mL buffer) will serve as indication for colonoscopy to be performed. Participants will also receive instructions for home use of the kit, and they will be notified that they must deliver it to the laboratory within 7 days. To perform the test it will not be necessary to follow a diet or restrict the use of drugs. For analysis a participant will be considered compliant if at least one FIT is handed in to the laboratory.

#### Other study variables:

Index case: Sex and age at diagnosis of CRC, lesion location and the anatomopathological result will be recorded.

Family tree in first generation (parents, children or siblings): deceased FDRs and age of living FDRs will be identified. FDRs with colorectal neoplasia will be identified.

FDR epidemiological data: age, sex, rural/urban location, substance abuse, history of CRC or adenoma or both, medical history, history of NSAIDs treatment, aspirin, or anticoagulants will be recorded.

Complications: Serious complications that occur during colonoscopy (those that result in the early termination of the procedure): immediate and delayed post-polypectomy hemorrhage and intestinal perforation will be recorded.

All the study variables will be recorded in an online database provided by the Spanish Gastroenterological Association, a member of the RedCap consortium. This application developed by Vanderbilt University guarantees data confidentiality.

### Statistical analysis plan

Screening uptake and detection rate of advanced neoplasia will be assessed by intention-to-screen analysis. First-degree relatives who will not attend the initial appointment and thus do not provide information about exclusion criteria will be considered as eligible and will be included in the analysis. Non-compliers for the assigned strategy will not be allowed to change to the other group. Between- group comparisons of the main outcomes will be calculated by multivariable logistic-regression analysis with adjustment for age, gender, and centre, and results were reported as odds ratios (OR) with 95% confidence intervals.

Comparisons of continuous variables were performed using the Mann–Whitney U-test. Categorical variables with two categories were compared using the χ^2^ test. All analyses were performed using SPSS statistical software version 25.0.

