Study groups: 1) annual FIT over three years (cutoff ≥ 10 μg Hb/g faeces to indicate colonoscopy); and

2) straightforward colonoscopy.

The recruitment process will be programmed through the index case, that will be interviewed to obtain their CRC family history. FDR will be contacted to make an appointment in the High-risk CRC Clinic of the participant centres. Randomization (1:1) will be performed before signing the informed consent to avoid selection bias. A researcher will be responsible to provide detailed information about the study and getting the informed consent. In case of willingness to participate in the study, the FDR will be randomized to one of the following arms: A) One-time colonoscopy; B) annual FIT (Automated quantitative Fecal Immunochemical Test) for three screening rounds and a colonoscopy in case of a positive FIT (cut-off = 10 μg Hb/g faeces). Screening uptake will be defined as the percentage of FDR who participate at least in one of the three FIT screening rounds in the FIT group or who undergo colonoscopy in the other group. Screening uptake will be calculated under the assumption of intention to screen analysis. Detection rates of advanced colorectal neoplasia will be assessed by as-screened analysis.

Sample size calculation

Assuming adherence rates of 0.60 vs 0.50 for FIT and colonoscopy, respectively, an alpha risk = 0.05, a beta risk = 0.10, in two-side tails, 538 FDR are required per group. The recruitment process will be programmed through the index case.

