### Sample size calculation.

The study was designed to achieve a 90% power and 95% confidence level for detecting an increase in the proportion of first-degree relatives undergoing CRC screening of 10% (from 50% in the colonoscopy arm to 60% in the FIT arm). According to these assumptions and considering that up to 5% participants in each group would be lost to follow-up, the estimated sample size was 1076 individuals (538 per arm).

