### Statistical Plan Analysis (page 10)

- 1. **Multiple regression analysis**

To assess screening uptake and advanced colorectal neoplasia multivariable logistic- regression analysis was performed with adjustment for age, gender, and centre. Age was categorized as having more or less than 54 years of age, according to the median age of participants. In addition, centres were categorized as high or low recruiters, if they included

more or less than 80 eligible individuals in the study, respectively. The detection rate of advanced colorectal neoplasia was the number of subjects with true positive results divided by the number of eligible subjects.

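### Relatives of one index case are powered and analysed as independent, and the randomisation unit is not stated; a model clustered on the index case would protect the inference under either unit

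*Supplement*

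**What the plan says.** Under the heading on selection and screening invitation, once an index case agrees, "a family tree of the first generation (parents, children or siblings) will be generated to identify all eligible and living FDRs". Randomisation follows at that stage, and all the relatives identified are then written to. No rule limits entry to one relative per family.

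The statistical analysis plan states that "comparisons of the main outcomes will be calculated by multivariable logistic-regression analysis with adjustment for age, gender, and centre". Amendment 3 revisits this model (it begins "To assess screening uptake and advanced colorectal neoplasia multivariable"), defines how age and centre are categorised, and keeps the same covariates. Neither text mentions a family term, random effect, GEE or cluster-robust variance.

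On sample size: "The study was designed to achieve a 90% power and 95% confidence level", for a change "from 50% in the colonoscopy arm to 60% in the FIT arm", and "considering that up to 5% participants in each group would be lost to follow-up". The Executive Summary gives the same target: "an alpha risk = 0.05, a beta risk = 0.10, in two-side tails, 538 FDR are required per group". No design effect, family size or ICC appears.

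**The concern.** Members of one family share an index case, a hospital, a coordinator's letters and probably attitudes to screening, so their uptake is likely to be correlated. For advanced neoplasia the protocol's own Background supports correlation: it cites risks that vary with the age of the index case and the number of affected relatives, both of which are family-level factors.

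Whether this matters for the treatment comparison depends on the unit of allocation. If a whole family goes to one arm, the effective sample size is below the head count, and a model that ignores family gives standard errors that are too small. If each relative is allocated separately, the correlation largely cancels from the between-arm contrast. The plan neither names the unit nor uses a model that is safe under both.

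The trial stopped for futility, so its message is a null result, and the width of the interval decides which differences remain compatible with the data.

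**Working it through.** **Inputs from the documents.** Uptake 50% v 60%, two-sided alpha 0.05, power 90%, 538 per arm (Executive Summary; Sample size calculation). Interim data: FIT 158/439, colonoscopy 147/431, OR 1.12 (0.84 to 1.49), p = 0.43 (Amendment 1).

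**Assumed, because the documents give neither.** Relatives per family m = 2 to 3; ICC = 0.1 to 0.3.

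**Step 1: reproduce 538.** With pooled proportion 0.55, n = [1.960·√(2·0.55·0.45) + 1.282·√(0.25 + 0.24)]² / 0.10² = 518.04, so 519. The continuity correction (n/4)·[1 + √(1 + 4/(n·0.10))]² gives 537.9, so 538 per arm exactly, before any allowance for loss. Without the correction, 519/0.95 = 547, which is close. Both routes treat subjects as independent (design effect 1).

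**Step 2: families allocated together.** Design effect DE = 1 + (m − 1)·ICC. The lowest case is 1 + 1·0.1 = 1.1 and the highest 1 + 2·0.3 = 1.6. Power is the two-proportion power at n/DE. The true size of the unclustered 5% test is 2·[1 − Φ(1.96/√DE)].

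| DE | 538/DE | Power, 538 per arm | Power, 439 and 431 | Size of nominal 5% test |
|---|---|---|---|---|
| 1.0 | 538 | 91.0% | 84.4% | 5.0% |
| 1.1 | 489 | 88.3% | 80.8% | 6.2% |
| 1.3 | 414 | 82.5% | 74.0% | 8.6% |
| 1.6 | 336 | 74.2% | 65.0% | 12.1% |

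Unequal family sizes raise the lower end. Simulating about 870 relatives in families of 1 to 4 gave rejection rates under no effect of 7.9%, 8.8% and 11.8% at ICC 0.1, 0.2 and 0.3. Cluster-robust standard errors gave 4.7 to 5.6%.

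**Step 3: relatives allocated singly.** In the same kind of simulation the unclustered test rejected in 4.8 to 5.5% of runs. A separate simulation with equal families of 2 or 3 and ICC 0.1 to 0.5 gave type I error of 4.5 to 5.7% and power of 90 to 91%. The planned inference is then sound, and what is lost is precision. The information gained by weighting with an exchangeable correlation ρ is approximately [1 + (m − 2)ρ] / [(1 − ρ)(1 + (m − 1)ρ)]:
- m = 2: 1.01, 1.04 and 1.10 at ρ = 0.1, 0.2 and 0.3;
- m = 3: 1.02, 1.07 and 1.16.

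With mixed families of 1 to 4 (ICC 0.2 to 0.3), simulation gave gains of about 4 to 12%.

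**Step 4: the interim interval, if families were allocated together.** SE of log OR = (ln 1.49 − ln 0.84)/3.92 = 0.146; ln 1.12 = 0.113. Multiplying the SE by √DE gives 0.81 to 1.55 (p about 0.50) at DE 1.3, 0.78 to 1.61 (p about 0.54) at DE 1.6, and 0.75 to 1.68 (p about 0.58) even at DE 2.0.

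**The case against.** The strongest reply is that the documents point to single allocation. The Executive Summary has the relative being randomised to an arm. The invitation procedure speaks of the option assigned to the individual. The sample size counts individuals, the futility section counts randomised relatives, and the design is described as parallel-group with no mention of clusters. The remark that randomisation takes place once the family tree is drawn fixes its timing, not its unit. On that reading, Step 3 shows that type I error and power are about as stated.

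This largely stands. A reader might infer from the missing family term that the primary interval, p value and 90% power are wrong. The documents do not support that, because it holds only under family allocation, which no section states. The reply does not close the matter, however: no section says that relatives of one index case are allocated independently of each other, and the plan's standard errors rest on it.

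A second reply is that every adjusted figure rests on an assumed family size and ICC. That is correct. In a milder case (m = 1.5, ICC 0.05) DE is 1.025 and power at 538 per arm is 90.4%.

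**Conclusion.** The omission is certain; its consequence is conditional. Several relatives of one index case can enter, and both the sample size and the model treat them as independent.

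- **Families allocated together** (m = 2 to 3, ICC 0.1 to 0.3, assumed): the interval is too narrow and the p value too small. Power at 538 per arm is 88% down to 74%. The nominal 5% test has a true size of about 6 to 12%, or 8 to 12% with unequal family sizes.
- **Relatives allocated singly**, the reading the wording favours: the planned inference is essentially valid, and a clustered model brings only a modest gain in precision.

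Two further inferences should be resisted. Clustering would not turn the interim null result significant; it could only widen the interval and so weaken a claim of similar uptake. Nor does a clustered model solve everything under single allocation: relatives whose letters name different tests may influence each other, and a corrected variance does not remove that contamination.

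This is a worthwhile, cheap improvement rather than a demonstrated error.

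**What to change.** 1. Fit the same logistic model, adjusted for age, gender and centre, by GEE with the index case as cluster (exchangeable working correlation, robust standard errors), for both uptake and advanced neoplasia. The standard errors are then valid under either unit of allocation.
2. State whether relatives of one index case were allocated together or singly. If singly, acknowledge possible contamination between relatives in different arms as a limitation that the model does not address.
3. Report the number of index cases, the relatives per index case and the estimated ICC.
4. Restate the power with a design effect only if families were allocated together.

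A sensitivity analysis restricted to families whose members share one arm is not advised. Under single 1:1 allocation only about half of two-member families (2 × 0.5²) and a quarter of three-member families (2 × 0.5³) would agree by chance, so it would discard much of the sample and over-represent small families.

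The cost is a few lines of analysis-plan wording and a different procedure in the same software. Index-case and family-tree data are already listed among the recorded variables. If families were the unit, the interval will widen and the stated power will fall.

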### Sample size calculation.

The study was designed to achieve a 90% power and 95% confidence level for detecting an increase in the proportion of first-degree relatives undergoing CRC screening of 10% (from 50% in the colonoscopy arm to 60% in the FIT arm). According to these assumptions and considering that up to 5% participants in each group would be lost to follow-up, the estimated sample size was 1076 individuals (538 per arm).

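### The same 538 per arm is given once without loss and once as already allowing for up to 5% loss; the arithmetic fits the no-loss reading, and the effect on power is small

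*Supplement*

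**What the plan says.** The sample size is justified in two places in the Supplement.

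- **Executive Summary, sample size paragraph.** The rates are given as "Assuming adherence rates of 0.60 vs 0.50 for FIT and colonoscopy, respectively", and the error levels and result as "an alpha risk = 0.05, a beta risk = 0.10, in two-side tails, 538 FDR are required per group". Loss is not mentioned.
- **Research Methodology, Sample size calculation.** "The study was designed to achieve a 90% power and 95% confidence level", for a rise "from 50% in the colonoscopy arm to 60% in the FIT arm". The number is then given with a loss allowance: "considering that up to 5% participants in each group would be lost to follow-up, the estimated sample size was 1076 individuals (538 per arm".

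Neither place names a formula or says whether a continuity correction was used. The Statistical analysis plan section analyses uptake by intention to screen. It keeps as eligible those relatives who never attend the first appointment, and it compares the arms by adjusted logistic regression.

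**The concern.** With rates, error level, power and allocation unchanged, adding a 5% loss allowance must raise the number to be randomised. Here it leaves the number at 538. Either the Executive Summary omits an assumption, or the later section claims an allowance that the number does not contain. A reader cannot tell from the text whether 538 is the number to randomise or the number to analyse. If it is the number to analyse, the planned power under the stated loss is slightly below the 90% quoted for the primary outcome.

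**Working it through.** **Inputs.** p1 = 0.50 (colonoscopy) and p2 = 0.60 (FIT), so d = 0.10 and p̄ = 0.55. Two-sided alpha 0.05 (z = 1.960) and power 90% (z = 1.2816), from both sample size statements. Allocation is 1:1 (Executive Summary). Loss is up to 5% per arm (Sample size calculation only).

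**Step 1: reproduce 538.**

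Pooled, uncorrected:
n = [1.960·√(2·0.55·0.45) + 1.2816·√(0.50·0.50 + 0.60·0.40)]² / 0.10² = (1.3790 + 0.8971)² / 0.01 = 518.0

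Continuity-corrected:
n' = (n/4)·[1 + √(1 + 4/(n·d))]² = (518.0/4)·[1 + √(1 + 4/51.80)]² = 537.85, rounded up to **538**

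The plan's figure is therefore matched to the integer, with no loss term.

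**Step 2: add the 5% allowance, n/(1 − 0.05).**

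| Two-sided formula | No loss | Divided by 0.95 | Rounded up |
|---|---|---|---|
| Unpooled | 514.9 | 542.0 | 542 |
| Pooled | 518.0 | 545.3 | 546 |
| Arcsine | 518.3 | 545.6 | 546 |
| p̄ variance throughout | 520.1 | 547.5 | 548 |
| Continuity-corrected | 537.85 | 566.2 | 567 |

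Rounding the base up before dividing adds one in each uncorrected row (543, 547, 547, 549). The shortcut of multiplying by 1.05 gives 540.6 unpooled, 543.9 pooled, 546.1 with p̄ variance and 564.7 corrected. All of these exceed 538. One-sided versions give about 420 to 442 before loss and 443 to 466 after, so they do not match either.

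**Step 3: work backwards.** 538 × 0.95 = 511.1, so 511 analysed per arm. The smallest two-sided requirement in the table is 515.

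**Step 4: power for 50% against 60%.** The formula is Φ{[d − c − 1.960·√(0.495/n)] / √(0.49/n)}, with c = 0 uncorrected and c = 1/n corrected.

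| Analysed per arm | Uncorrected | Corrected |
|---|---|---|
| 538 | 91.0% | 90.0% |
| 511 | 89.6% | 88.4% |

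For n = 511 uncorrected: (0.10 − 0.0610)/0.03097 = 1.259, and Φ(1.259) = 0.896.

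Against the stated 90%, the shortfall at 511 is 0.4 points uncorrected or 1.6 points corrected.

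**The case against.** The strongest reply is that the continuity correction is a guess. No formula is named, and the planned logistic regression uses no such correction. Without it, 538 does contain some room: (538 − 515)/538 = 4.3% on the unpooled formula, or (538 − 518)/538 = 3.7% on the pooled one. A full 5% allowance would add only 4 people per arm (542) or 8 (546). This stands to the extent that the loss statement cannot be called wrong outright. It does not restore the statement, because no two-sided route tried reaches 538 with 5% loss, while one reaches it to the integer without.

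A second reply is that the Executive Summary may simply have left the loss clause out. That is possible, but the longer section should then be reproducible with the clause in, and it is not.

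A third reply is that loss scarcely applies, because relatives who do not attend stay in the denominator. This is largely right, and it limits the effect on power. It does not make the allowance meaningless. Randomisation precedes consent, the exclusion criteria include declining to sign, and the plan does not say whether attenders found ineligible are kept. Some loss from the denominator is therefore possible.

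A reader might go further and infer that the trial was designed underpowered, or that the stop at 870 belongs to this point. The documents support neither. Power at 538 analysed is 90.0% to 91.0%. Amendment 1 reports the stop openly, and the futility section of Amendment 3 gives conditional power (2.95%) and predictive power (0.29%). Those figures have no bearing on whether 538 contains a loss allowance.

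**Conclusion.** The two sample size statements disagree on whether 538 per arm includes a 5% loss allowance, and the arithmetic favours the reading that it does not. This is a documentation and arithmetic inconsistency in the justification for the primary outcome, not a material loss of power. At worst, with the full 5% lost from the analysis, power is 88.4% to 89.6% instead of 90%. In the likelier case, with non-attenders retained, 538 gives the power stated.

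The conclusion assumes the stated rates of 50% and 60%, two-sided 5% and equal allocation. It reads those rates as uptake among all randomised relatives. The continuity correction is inferred from the exact match and needs the authors' confirmation. The disagreement between the two sections does not depend on it.

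**What to change.** Make the Executive Summary and the Sample size calculation section agree, and name the formula, including whether a continuity correction was applied. Then choose one of two wordings:

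- **Remove the loss clause**, and present 538 per arm as the number for 90% power with no allowance, noting that relatives who do not attend remain in the intention-to-screen denominator; or
- **Keep the clause**, say which relatives it covers (for example, attenders found ineligible), and restate the power as about 88% to 90% with 511 analysed per arm.

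The cost is a few sentences. The target, the analysis and the conduct of the trial do not change, and no additional enrolment is needed. Under the second option the quoted power becomes slightly less favourable.
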